**Mood and Social Interaction Data**

In this study, the mood will be assessed using the DASS scale, and social interaction will be measured using the Berkman-Syme SNI. The baseline measures for the 2 groups will be compared using analysis of variance. In addition, changes in these measures over time will be compared for the 2 groups of respondents using an ITT RMMM, controlling for age, gender, and education level and any variable that differs markedly between the groups at the baseline.

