### Study Hypotheses

In comparison to the long-term hearing aid users, after wearing a hearing aid for 6 months, the group who have never worn a hearing aid will exhibit improved cognition, reduced depression, improved social interaction, altered activation of the auditory cortices and attendant networks, and altered connectivity between auditory and attendant networks.

In addition, the study will explore any baseline relationships among the cognition, psychosocial, and neural function in participants with and without a hearing aid and any relationships among the improved cognition, psychosocial function, and neural function in participants without a hearing aid after the hearing aid intervention, as seen in Figure 1.

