## Methods

### Study Design

The study is a prospective cohort design evaluating the effect of the hearing aid use on cognition, psychosocial factors (eg, depression and social interaction), and neural function. We will recruit 2 participant groups of similar size consisting of people with mild to moderate SNHL. Of note, group randomization is not possible in this study; however, the groups will be matched as much as possible in terms of the degree of hearing loss.

Group A: Patients with SNHL who have used hearing aids for, at least, the previous 12 months and plan to continue using their hearing aids for the next 6 months.Group B: Patients with SNHL who have never used hearing aids before and who will be willing to wear hearing aids for the next 6 months.

All participants would be asked to complete, at 2 time points (t) including baseline (t=0) and follow-up (t=6 months), tests of hearing and psychosocial and cognitive function and attend an MRI session.

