#### Cognitive Data

The SUCCAB performance measure for spatial working memory will be used as the primary SUCCAB measure; this measure has been found to be particularly effective in measuring short-term changes in cognition of the elderly [52] and is calculated by dividing the response accuracy by the reaction time for a spatial working memory task. Using this and other SUCCAB performance measures, baseline values for the 2 groups will be compared using an ANCOVA analysis, controlling for age, gender, and education level. In addition, changes in these values over time will be compared for the 2 groups of respondents using an ITT RMMM, controlling for age, gender, and education level and any variable that differs markedly between the groups at the baseline.

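### The baseline mood and social-network comparison of two non-randomised groups is unadjusted, unlike the cognitive one, and so is open to confounding by age, gender and education

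*Protocol article*

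**What the plan says.** Three statements under Primary Statistical Analyses set the models.

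- Cognitive Data, baseline: "baseline values for the 2 groups will be compared using an ANCOVA analysis, controlling for age, gender, and education level".
- Mood and Social Interaction Data, baseline: "The baseline measures for the 2 groups will be compared using analysis of variance". No covariates follow.
- Mood and Social Interaction Data, change over time: an intention-to-treat repeated measures mixed model, "controlling for age, gender, and education level and any variable that differs markedly between the groups at the baseline".

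Study Design describes who is compared. Group A is "Patients with SNHL who have used hearing aids for, at least, the previous 12 months". Group B is "Patients with SNHL who have never used hearing aids before and who will be willing to wear hearing aids for the next 6 months". It states that "group randomization is not possible in this study" and that "the groups will be matched as much as possible in terms of the degree of hearing loss". No other matching variable is named.

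Study Hypotheses places the psychosocial claim at follow-up: "after wearing a hearing aid for 6 months, the group who have never worn a hearing aid will exhibit improved cognition, reduced depression". Baseline relationships among cognition, psychosocial and neural function are described there as something to explore.

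**The concern.** The article names a model for each baseline comparison, and the two models differ without a stated reason. The very next sentence on mood and social interaction adjusts the same outcomes for age, gender and education, so the omission is not a general view that these outcomes need no adjustment.

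The exposure is plausible from the article alone. The eligible age range is 55 to 90 years, and age, gender and education are not matched. The Introduction describes hearing loss as progressive and says people often take about 10 years to recognise a hearing problem and act on it. Established users may therefore be older than never-users. The SNI covers relationships such as spouse, parents and workmates. That their availability varies with age is a reasonable expectation, though the article does not say so.

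At stake is the reading of a baseline difference in DASS or SNI. Without adjustment, a difference between users and never-users could be put down to hearing aid use when it reflects only who is in each group. The comparison sits among the primary analyses and is not labelled descriptive. The Results section also gives baseline analyses their own completion date, so they could be reported separately.

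**Working it through.** **Inputs from the article.** 30 per group, 5% level, 80% power and a detectable baseline effect of d=0.63 (Study Power Analysis, for spatial working memory only). Covariates are age, gender and education, so k=3. No detectable effect is given for DASS or SNI.

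**The plan's own figure.** Take a two-sided test with df = 2n − 2 − k = 60 − 2 − 3 = 55 and noncentrality (d/√(1 − R²)) × √(n/2), where R² is the share of outcome variance explained by the covariates. With d=0.63:

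- R²=0: power 66.9%
- R²=0.27: power 80.1%

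The figure is attainable if the covariates explain about 27% of the variance. R² is not stated, so d=0.63 is not called wrong. It also concerns cognition and does not settle the psychosocial comparison.

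**Bias of the unadjusted comparison.** Suppose there is no group difference at equal covariate values. If one covariate differs between groups by g within-group SDs and has within-group correlation r with the outcome, the unadjusted difference is g × r outcome SDs. The rejection rate comes from the noncentral t distribution with 58 df and noncentrality g × r × √(30/2). Both g and r are assumptions.

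| Gap g (SD) | Correlation r | Spurious d = g × r | Rejection at nominal 5% |
|---|---|---|---|
| 0.25 | 0.1 | 0.025 | 5.1% |
| 0.5 | 0.3 | 0.15 | 8.8% |
| 0.75 | 0.3 | 0.225 | 13.7% |
| 0.8 | 0.4 | 0.32 | 23.0% |
| 0.75 | 0.5 | 0.375 | 29.8% |

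The problem is negligible at the top of the table and material at the bottom.

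**Cost of adjusting.** Effect detectable with 80% power, two-sided 5%, 30 per group:

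| Model | R² | Detectable d |
|---|---|---|
| Analysis of variance | – | 0.736 |
| ANCOVA, 3 covariates | 0 | 0.736 |
| ANCOVA, 3 covariates | 0.10 | 0.699 |
| ANCOVA, 3 covariates | 0.20 | 0.659 |
| ANCOVA, 3 covariates | 0.27 | 0.629 |

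These values take the covariates as balanced between groups. A gap of g SDs in one covariate multiplies the variance of the adjusted difference by about 1 + g²/4. For g=0.5 this is 1.0625, a standard error about 3% larger. For g=0.8 it is 1.16, about 8% larger. That loss arises only where there is imbalance to correct.

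**The case against.** The strongest reply is that no hypothesis rests on this comparison. Reduced depression and improved social interaction are predicted after 6 months, and the model that tests them is adjusted. The sample size is not based on it either. This stands. A reader might infer that the 6-month psychosocial conclusions are compromised, but the article does not support that.

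A second reply is that a crude comparison has a proper use. It describes two groups known to differ in how they arose, and it can help to find variables that differ markedly at baseline for the longitudinal model. This stands in part: an unadjusted comparison is sound if labelled descriptive. The article does not label it so, and the same reasoning would apply to cognition, which is adjusted.

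A third reply is that confounding is not shown. This also stands. A reader might infer that the comparison is confounded, but the article reports neither an imbalance nor a covariate–outcome correlation, and at the low end of the assumed range the error rate is essentially nominal. Three covariates would not remove self-selection in any case.

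A fourth reply is that a condensed article leaves covariates to a fuller document. This does not answer the point, because the article fixes a method here, and fixes a different one for the parallel comparison.

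**Conclusion.** The point holds as an unexplained inconsistency that leaves the baseline DASS and SNI comparison open to confounding by age, gender and education. The possible false-positive rate runs from about 5% to about 30% at a nominal 5%, over gaps of 0.25 to 0.8 SD and correlations of 0.1 to 0.5. All of these gaps and correlations are assumptions, and each case treats a single covariate. The consequence is confined to inference from the baseline comparison. It is a modest point, worth correcting because the better method is already in the plan.

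**What to change.** Under Mood and Social Interaction Data, replace the baseline analysis of variance with the ANCOVA already specified for baseline cognition, controlling for age, gender and education level. State that any unadjusted comparison of DASS or SNI is descriptive only.

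This changes one sentence, uses covariates already in the plan, needs no extra participants and costs about 3 degrees of freedom out of 58. No further covariate is needed to resolve the inconsistency. Adding a measure of hearing level, for example, would need its own argument, since degree of hearing loss is already the matching variable.

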**Neuroimaging Data**

Inferences from functional and structural neuroimaging analyses will be assessed using the random field theory to correct for multiple comparisons at the cluster level.

##### Speech Processing Task Data: Functional Alteration

First, we will compute the contrast of MAT>NOS (NOS controls for viseme processing) for each participant and enter the contrasts into an RMMM to assess the effect of the first-time hearing aid use on speech sound processing; (2) we will assess changes in the functional connectivity in key areas determined from this analysis using the generalized psychophysiological analytic approach [63]; (3) finally, we will use key areas of difference as seeds in the functional connectivity analysis of the resting state data.

Secondly, we will compute the contrast of NOS>CON (CON controls for basic face motion processing) for each participant and enter the contrasts into an RMMM to assess the effect of the hearing aid use on viseme processing; (2) we will assess changes in the functional connectivity in key areas determined from this analysis using the generalized psychophysiological analytic approach [63]; (3) finally, we will use key areas of difference as seeds in the functional connectivity analysis of the resting state data.

##### Structural T1 Data: Structural Alteration

To assess plastic alteration in response to the first-time hearing aid use, these spatially smooth gray matter images will be entered into an RMMM.

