### Eligibility Criteria

Participants must be aged 55-90 years, speak English as first language, exhibit mild or moderate SNHL with a PTA of thresholds at 0.5-4 kHz in both ears, willing to undergo two 1-hour MRI scanning sessions over a period of 6 months, and willing to wear hearing aids for 6 months or must have been wearing hearing aids for at least 1 year. Furthermore, participants must give written informed consent.

Participants will be excluded if they exhibit left handedness, marked visual impairment that would prevent reading, cognitive impairment (defined as a score ≤23 on the Mini-Mental State Examination, MMSE), severe or profound hearing loss, and MRI contraindications. Figure 2 presents the flowchart of the overall data collection plan.

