### Primary Statistical Analyses

In this study, repeated measures mixed model group (no hearing aid vs hearing aid users) x Time (Time 1 vs Time 2) analysis (RMMM) will be used for all analyses. The missing data will be accommodated in this analysis; however, in the case of whole-brain fMRI analyses, only completed protocol participants will be included. In the ITT RMMM analyses, the autoregressive (AR) dependence will be assumed.

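### The primary imaging group-by-time models name no between-subject covariates, so an age imbalance between self-selected groups could pass for an effect of first-time hearing aid use

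*Protocol article*

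**What the plan says.** Study Design states that "group randomization is not possible in this study" and that "the groups will be matched as much as possible in terms of the degree of hearing loss". No matching on age, gender or education is stated. The age range is wide: "Participants must be aged 55-90 years" (Eligibility Criteria).

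Primary Statistical Analyses opens with one general model, group by time, and says that this "analysis (RMMM) will be used for all analyses". Only group and time are named there. It adds that "in the case of whole-brain fMRI analyses, only completed protocol participants will be included".

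The subsections then differ:

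- **Cognitive Data (primary):** change over time is compared "controlling for age, gender, and education level and any variable that differs markedly between the groups at the baseline".
- **Mood and Social Interaction Data:** the same covariate list is given for change over time.
- **Speech Processing Task Data:** for matched versus no sound, the plan is to "enter the contrasts into an RMMM to assess the effect of the first-time hearing aid use on speech sound processing". The no sound versus control contrast is handled in the same way. No between-subject covariate is given for either.
- **Structural T1 Data:** "these spatially smooth gray matter images will be entered into an RMMM". Again no between-subject covariate is given.

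The covariates mentioned for task fMRI under Magnetic Resonance Imaging Scan Acquisition are realignment and other noise terms within each participant's own time series. They do not address differences between the groups.

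**The concern.** One group chose to obtain hearing aids at least a year ago and the other never has. People who differ in that way may also differ in age and education, and the design does nothing stated to balance either. The article accepts this for two of its three outcome domains by naming covariates, and gives no reason why imaging should be treated differently.

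The Background says that people with hearing loss show faster brain atrophy than adults with normal hearing, so differential change is a possibility that the document itself raises. The structural analysis is nevertheless to be read as plastic change in response to first-time aid use. If one group is older and tissue or activation changes faster with age, part of the group-by-time effect is ageing. Any region found in this way would also carry forward, because the areas identified in the task contrasts serve as seeds for the connectivity analyses.

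**Working it through.** **1. The plan's own figure.** Study Power Analysis gives a detectable interaction of d = 0.77 with 27 per group, 5% significance and 80% power, for spatial working memory. The group size is 30 × 0.9 = 27. With a two-sided test of change, the normal approximation is (1.960 + 0.842) × √(2/27) = 0.762, and the noncentral t with 52 degrees of freedom gives 0.777. The figure reproduces. No power figure is given for imaging, so only the group size and the 5% level are taken from here.

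**2. What a covariate can do to the interaction.** With two visits and complete data, the group-by-time estimate equals the difference between groups in mean change. A covariate that shifts both visits equally cancels. A covariate with slope γ on change, and a mean gap between groups of Δ, biases the estimate by γ × Δ.

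Simulation with no true effect, 27 per group and an assumed age gap of 0.5 SD:

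| Assumed slope of change per SD of age | γ × Δ | Mean unadjusted estimate | Mean estimate with age × time |
|---|---|---|---|
| 0 | 0.00 | 0.00 | 0.00 |
| −0.1 | −0.05 | −0.05 | 0.00 |
| −0.2 | −0.10 | −0.10 | 0.00 |
| −0.3 | −0.15 | −0.15 | 0.00 |

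**3. Which form of adjustment matters.** One simulated complete data set was fitted three ways. The group-by-time estimate was 0.1827 with no covariate, 0.1827 with age as a main effect, and 0.300 with age × time. A main effect alone does not touch the estimate in completers.

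**4. Illustrative size for one scalar test.** The inputs are 27 per group (from the plan), two-sided 5% (the plan does not state sidedness), and an assumed within-group correlation r between the covariate and six-month change. The gap in SD units is also assumed. The unadjusted test keeps the covariate's variance in its denominator, so:

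- spurious d = r × gap
- noncentrality = d × √(27/2), with 52 degrees of freedom and critical value 2.007

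| r | Gap (SD) | Spurious d | Noncentrality | Rejection |
|---|---|---|---|---|
| 0.3 | 0.5 | 0.15 | 0.551 | 8.4% |
| 0.3 | 0.8 | 0.24 | 0.882 | 13.9% |
| 0.3 | 1.0 | 0.30 | 1.102 | 19.1% |
| 0.2 | 0.5 | 0.10 | 0.367 | 6.5% |
| 0.4 | 1.0 | 0.40 | 1.470 | 30.3% |

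The last two rows are the ends of the range for r from 0.2 to 0.4 and gaps from 0.5 to 1.0 SD.

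**The case against.** **Silence is not a decision.** This is a journal article, its imaging text is terse throughout, and second-level design covariates are often left to the full protocol. That is fair as far as it goes: a reader might infer that the investigators decided against adjustment, and the text does not say so. But the same article spells out the covariate set twice, for the other two domains under the same heading, and omits it for imaging. Run as written, the imaging models are unadjusted.

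**The contrast with the adjusted models is weaker than it looks.** This stands. The cognitive and mood models name no covariate × time terms. If controlling for age there means a main effect, step 3 shows that it would do nothing for the interaction among completers. A reader should not infer that those two domains are secure and imaging alone exposed, nor that copying their covariate wording into the imaging sections would be enough.

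**Hearing loss.** A reader might list it as an equally neglected confounder. The document does not support that. It is the one variable matched by design, eligibility restricts it to mild or moderate loss, and no model names it, so there is no inconsistency between domains. Under Auditory Stimuli Input Considerations, sound is tailored to each participant's audiogram, and the no sound versus control contrast contains no sound. It matters only if matching fails.

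**The rejection rates.** A reader might take the 8% to 19% as the study's false-positive rate. They are not. The correlation and gaps have no source in the document, the low end is close to 5%, and the calculation is for one scalar test, whereas Neuroimaging Data specifies cluster-level random field correction. That correction controls multiplicity; it does not remove bias.

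**Gender and education.** The document gives no specific reason to expect either to drive six-month imaging change. Age is the main concern; the other two are included for consistency with the other domains.

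**Conclusion.** The concern holds in a limited form. The three primary imaging models (two task contrasts and gray matter) name no between-subject covariates in a non-randomised comparison with a 35-year age span (90 − 55), although the article lists age, gender and education elsewhere for the same kind of model. An imbalance in age that also predicts six-month change would be read as an effect of first-time aid use.

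Two conditions are needed, an imbalance and a relation with change, and the document establishes neither. Under moderate assumed values the spurious effect is 0.15 to 0.30 SD of change. For scale, the plan's detectable interaction for cognition is 0.77, so bias of this kind would more often distort an estimate than create a finding on its own. It is worth correcting because the remedy is nearly free. The document does not support the stronger statement that the imaging results will be confounded.

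**What to change.** In each primary imaging model (matched versus no sound, no sound versus control, gray matter), analyse the Time 2 minus Time 1 image with group as the factor and age, gender and education as covariates. The equivalent within the stated mixed model is to add covariate × time terms. Say explicitly that main effects alone are not what is meant.

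Add baseline pure tone average if matching leaves the groups different on it, with the rule for that written down before the images are analysed. Use the same covariate set in all three models.

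The cost is three degrees of freedom, or four with pure tone average, out of 27 + 27 − 2 = 52, counting education as a single term. No new data are needed: age, gender and education are already planned covariates, and audiometry is done at baseline. The change amounts to a sentence or two in the neuroimaging part of Primary Statistical Analyses.

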### Exploratory Analyses

#### Cognitive Data

Correlations between the SUCCAB performance measures and neuroimaging data will be investigated at the baseline and after 6 months for each o group using ANCOVA analyses and ITT Hierarchical Linear Model analyses.

#### Psychosocial Data

Correlations between DASS and the Berkman-Syme SNI with the SUCCAB performance measures and the neuroimaging data will be investigated at the baseline and after 6 months for each group using ANCOVA analyses and ITT Hierarchical Linear Model analyses. In addition, structural equation modeling will be used to explore the role of the mood and social interaction data as process variables for the effects of hearing aid use on the cognition and neural function, testing the hypothesized model shown in Figure 1.

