**Conclusions:**

This is the first study to assess the effect hearing aid use has on neural, cognitive, and psychosocial factors in individuals with SNHL who have never used hearing aids. Furthermore, this study is expected to clarify the relationships among altered brain structure and function, psychosocial factors, and cognition in response to the hearing aid use.

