#### Follow-Up Periods After the Baseline Data Collection

During the 6-month waiting period between MRI scans, phone call and email reminders for the second testing session will be sent to all participants at 1, 3, and 5 months. At the same time, counseling and other compliance-improving policies [44-46] will be provided to ensure that participants are wearing their hearing aids. In addition, follow-up checks will be conducted by the audiology clinics every 6 weeks for first-time hearing aid users, during which hearing aid usage data will be downloaded and hearing aids will be restarted. An automatic internet-based data logging function installed in the hearing aids will be used to collect hearing aid usage data, which will be used to monitor and assess hours of hearing aid use by these participants. Furthermore, all participants will be encouraged to set their own goals for the hearing aid use and will be asked to assess how well these goals have been met on a regular basis.

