### Outcomes

#### Assessments for Study

The assessments selected in this study are categorized as follows: hearing assessments, demographic questionnaire, hearing aid benefit questionnaire, cognitive performance, mood and social interaction assessments, and MRI scanning. All participants enrolled in this study will complete these assessments at the baseline and again after 6 months.

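### The exploratory structural equation model cannot show that mood or social change comes before cognitive or neural change, because all are measured at the same two visits

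*Protocol article*

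**What the plan says.** Under Exploratory Analyses, Psychosocial Data, the protocol article states that "structural equation modeling will be used to explore the role of the mood and social interaction data as process variables". Hearing aid use is the exposure in this model, and cognition and neural function are the outcomes. The same sentence describes the purpose as "testing the hypothesized model shown in Figure 1". The figure itself is not reproduced in the text available.

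The timing of measurement is fixed in two places. Study Design has participants complete, "at 2 time points (t) including baseline (t=0) and follow-up (t=6 months), tests of hearing and psychosocial and cognitive function", together with an MRI session. Assessments for Study says of the whole battery (hearing, cognition, mood, social interaction, MRI): "All participants enrolled in this study will complete these assessments at the baseline and again after 6 months".

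Between these visits, Follow-Up Periods After the Baseline Data Collection describes contacts but no mood, social or cognitive measure. It says that "phone call and email reminders for the second testing session will be sent to all participants at 1, 3, and 5 months". First-time users also attend clinic checks every 6 weeks, "during which hearing aid usage data will be downloaded and hearing aids will be restarted". That is a record of exposure, not of a mediator or an outcome.

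Study Design also states that "group randomization is not possible in this study". The Abstract's Conclusions say that "this study is expected to clarify the relationships among altered brain structure and function, psychosocial factors, and cognition in response to the hearing aid use".

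**The concern.** A process variable has to change after the exposure and before the outcome. In Group B the exposure does come before the 6-month measures. However, mood or social interaction (the proposed process) and cognition or brain function (the outcome) are each seen once after fitting, at the same follow-up. Three explanations then leave much the same trace in the data:

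- hearing aid use improves mood, and mood improves cognition;
- hearing aid use improves cognition, and cognition improves mood;
- hearing aid use affects both separately, and the two changes are correlated for another reason, such as the participant's state at the visit.

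A significant indirect path would be consistent with all three. At stake is the mechanism statement: a paper could name mood or social interaction as the route of benefit when the data do not distinguish it from the alternatives. The Limitations section does not mention this.

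**Working it through.** **1. The plan's own figure.** Study Power Analysis gives 27 per group at follow-up (30 × 0.9), a 5% level, 80% power and a detectable group-by-time effect of d = 0.77. Taking the test as two-sided:

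- power = Φ(0.77 × √(27/2) − 1.960) = Φ(2.829 − 1.960) = Φ(0.869) = 0.81, or 0.79 with the noncentral t;
- detectable d = (1.960 + 0.842) × √(2/27) = 0.76, or 0.78 with the noncentral t.

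The figure reproduces. It is a detectable effect, given in a section that works with spatial working memory. No figure is given for mood, social interaction or the structural equation model.

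**2. Set-up (assumed values).** Let a be the group effect on mood change in SD units and r the residual correlation between mood change and cognitive change. The true indirect effect is zero. An indirect effect is declared when both paths reach p < 0.05: group to mood, and mood to cognition given group.

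**3. Approximation by hand.** The two path tests are close to independent, so the false-mediation rate is roughly the product of their powers.

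- Path 1: Φ(a√13.5 − 1.960), with √13.5 = 3.674. For a = 0.3, 0.5 and 0.77 this is 0.195, 0.451 and 0.808. For a = 0 it is 0.05.
- Path 2 (Fisher z, 54 participants, one covariate): Φ(atanh(r) × √50 − 1.960). For r = 0.2, 0.3 and 0.5 this is 0.299, 0.590 and 0.973.

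**4. Products, with simulated rates in brackets** (27 per group, 3,000 trials per cell):

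| Mood effect a | r = 0.2 | r = 0.3 | r = 0.5 |
|---|---|---|---|
| 0 | 1% (1%) | 3% (3%) | 5% (5%) |
| 0.3 SD | 6% (5%) | 12% (12%) | 19% (19%) |
| 0.5 SD | 13% (13%) | 27% (26%) | 44% (42%) |
| 0.77 SD | 24% (23%) | 48% (47%) | 79% (77%) |

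Repeat runs move single cells by about a point. The summary ranges are about 5–18%, 13–43% and 24–77%. A Monte Carlo confidence interval for the indirect effect agrees within about 2 points. The Sobel test is lower (11%, 27% and 68% at a = 0.77). Baseline adjustment with an assumed stability of 0.6 is higher (27%, 54% and 90% at a = 0.77).

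**5. Reverse order.** If hearing aids improve cognition by 0.77 SD and cognition then drives mood with a path of 0.3 to 0.5, mediation through mood is declared in about 8–27% of trials.

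**6. Discrimination.** When mood truly mediates (0.77 SD, r = 0.2 to 0.5), the same test declares mediation in 24–78% of trials. That is almost the false rate in the last row of the table.

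**7. Model fit does not help if direct paths are included.** The forward model factors the joint density as f(M|G) × f(Y|M,G) and the reversed model as f(Y|G) × f(M|Y,G). These are the same density. On one simulated data set both log-likelihoods were −145.8395.

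**The case against.** Four points can be made for the plan.

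- *The indirect-effect test needs more than a concurrent correlation.* This stands. A reader might infer that the model rejects for any concurrent association. It does not: with no group effect on mood the rate is about 5% or below even at r = 0.5, although the mood-to-cognition path alone is then significant in 97% of trials.
- *The large rates rest on large assumed effects.* This stands too. A reader might take d = 0.77 as the plan's expected hearing aid effect. It is only the detectable effect for the group-by-time interaction and says nothing about mood or social scores; the sentence on the assumed effect is cut off in the available text. The documents therefore do not support saying that false mediation will occur often. They do make the condition relevant, since Study Hypotheses predicts reduced depression and improved social interaction in Group B.
- *The specification is not visible.* Correct. The article does not say whether the model uses change scores, concurrent values or lagged paths, or whether direct paths are included. A path from baseline mood to 6-month cognition kept the false rate at 5% or below in simulation. In Group B, though, that mood score is taken before fitting, so it cannot show a mood change produced by the aid.
- *The analysis is exploratory, and the Abstract speaks of relationships, not causal direction.* Correct. This limits the severity. It does not supply the missing order in time.

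**Conclusion.** The concern holds in a limited form. With all measures taken at two common visits, the structural equation model cannot establish that mood or social change precedes cognitive or neural change. If hearing aid use affects mood, a non-causal association at follow-up can be reported as mediation well above the 5% level. The excess is slight to moderate for a 0.3 SD mood effect and large only when both the mood effect and the correlation are large.

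The timing problem follows from the text alone. The rates rest on assumed effects and correlations, a concurrent change-score analysis, and 27 per group. Severity is minor: no primary analysis depends on this model, and the harm is confined to how a mechanism would be described.

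**What to change.** In Exploratory Analyses, Psychosocial Data:

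- Model mood or social change and cognitive or neural change as parallel outcomes of group, with a free residual covariance. Report that covariance as an association of changes.
- If the Figure 1 path model is kept, fit the reversed order (cognition or neural function to mood or social interaction) beside it and report both indirect effects with intervals.
- State that no direction or mediation is concluded from two simultaneous visits.

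The cost is a change of wording, one extra model and a weaker statement about mechanism.

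Adding mood and social questionnaires alone at the existing 3-month contact is not recommended as a cure. Without cognition measured at the same time, a persistent shared cause still links 3-month mood to 6-month cognition. With a 0.77 SD effect, r = 0.3 to 0.5 and an assumed stability of the shared cause between 0.5 and 1.0, false mediation was still about 16–79%.
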